# Efficacy of web-assisted self-help for parents of children with ADHD (WASH) – a three-arm randomized trial under field/routine care conditions in Germany

**DOI:** 10.1186/s12888-020-2481-0

**Published:** 2020-02-21

**Keywords:** Attention-deficit/hyperactivity disorder, Oppositional defiant disorder, Children, Web-based parent management training self-help intervention, e-health

## Abstract

**Background:**

Current clinical guidelines recommend parent management training (PMT) in the treatment of attention-deficit/hyperactivity disorder (ADHD) and oppositional defiant disorder (ODD). However, (a) a lack of supply and (b) structural barriers to attending and continuing face-to-face PMT restrict the access to this training. The main purpose of this study is to investigate the efficacy of online PMT in decreasing ADHD symptoms and oppositional behavior problems and to evaluate the effects of additional telephone-based support of the parents.

**Methods:**

The target sample size is *n* = 495 children with suspected or even clinical diagnosis of ADHD and current symptoms of ADHD or ODD. The study is based on a randomized three-arm parallel group design, in which the effects of treatment as usual (TAU) are compared to TAU plus web-assisted self-help (TAU+WASH) and to TAU plus web-assisted self-help and telephone-based support (TAU+WASH+SUPPORT).

**Discussion:**

The results will provide important insights into the efficacy of web-assisted self-help for parents of children with ADHD and the additional effects of telephone-based support.

**Trial registration:**

German Clinical Trials Register (DRKS) DRKS00013456. January 3rd 2018.

World Health Organization Trial Registration Data Set: Universal Trial number (UTN) U1111–1205-6181. November 23rd 2017.

## Background

Attention-deficit/hyperactivity disorder (ADHD) is one of the most common mental disorders in childhood and adolescence, with a worldwide prevalence of about 5% [1]. Children with ADHD have an increased risk for oppositional (oppositional defiant disorder, ODD), aggressive and antisocial behavior (conduct disorder, CD) problems, besides other comorbid conditions. There is evidence supporting the efficacy of parent management training (PMT) in the treatment of these behaviors. Meta-analyses found that PMT improves parenting and reduces ADHD symptoms and conduct problems in children with ADHD, as well as other externalizing behavior problems [2, 3]. Moreover, recent guidelines recommend behavior therapy (mainly PMT) as well as pharmacotherapy in children with ADHD [4–6]. Over the last few decades, the prevalence of pharmacotherapy has increased significantly across most countries, including Germany, although a downward trend has also emerged in recent years (e.g. [7]). However, the provision of behavioral interventions in Germany is not guaranteed, with strong regional variations. For example, Gebhardt et al. (2008) [8] examined a sample of children and adolescents with ADHD receiving pharmacotherapy, drawn from a German health insurance company, and found that only 19% had received PMT and 7% had received family therapy.

Media-applied PMT may help to overcome this structural lack of therapeutic supply as well as the structural barriers to attending and continuing face-to-face parent training, such as time and work commitments [9]. Telephone-assisted self-help interventions have been found to address some of these barriers and, furthermore, to be effective in the treatment of externalizing behavior problems [10, 11] and to be superior to treatment as usual [12]. Although studies have evaluated internet-based treatments for patients with different disorders [13], research on internet-based self-help for caregivers of children with ADHD is rare. According to a meta-analysis on self-help approaches for parents of children with externalizing behavior disorders [11], two studies on web-based training [14, 15] found small to medium effects (Cohen’s d = 0.42 to 0.72). A Finnish study on internet-based training with telephone counseling for parents of four-year-olds with externalizing behavior disorders found small effects (d = 0.35) [16]. Comparable effects between self-help programs based on self-help books and internet-based self-help programs were found, for example, in Australia [15] and Germany [17–19]. Moreover, self-help was found to enhance the effect of pharmacotherapy in a group of children with ADHD [10]. Recently, Ghaderi et al. [20] found web-based PMT to be as effective as face-to face PMT in children with ODD/CD (including ADHD).

The primary objective of the current study is to assess the efficacy of a newly developed web-assisted self-help program (WASH) for parents of children with ADHD aged 6–12 years. Specifically, the study assesses the efficacy, in terms of reducing externalizing symptoms (ADHD and ODD), of web-assisted parent self-help (WASH) and of WASH combined with additional telephone support (WASH+SUPPORT) compared to treatment as usual (TAU). *The main hypotheses are that (a) WASH + SUPPORT + TAU is more effective than WASH alone, and (b) WASH + TAU is more effective than TAU*. *Moreover, it is expected that face-to-face behavior therapy (ESCAschool) is more effective than WASH + SUPPORT.*

In addition, the following research questions are addressed: (c) acceptance and utilization of WASH compared to WASH+SUPPORT, (d) satisfaction of parents and referring health care providers (HCP, i.e. pediatricians or child and adolescent psychiatrists in their own registered practices) with this intervention, (e) effects of WASH and WASH+SUPPORT on comorbid mental disorders, psychosocial impairment and quality of life of the children as well as on parenting and parental stress, and (f) effects on the utilization of health care services. Furthermore, differential effects (moderators) and mediators of treatment outcome (e.g. sociodemographic variables, parenting and parental stress) are investigated.

## Methods/design

### Participants

Nationwide, all pediatricians as well as child and adolescent psychiatrists working in their own registered practices (*n* = 5015) are contacted, informed about the project and asked to refer patients to the study. Referral by HCPs takes place between December 2017 and February 2020.

To be registered, families have to meet the following inclusion criteria (as rated by the referring HCP): (i) child age 6;0 to 12;11 years; (ii) a (suspected) diagnosis of ADHD; (iii) current symptoms of ADHD or ODD; and (iv) sufficient German language skills of parents (main caregiver with a parenting role for the registered child). Exclusion criteria are: (i) diagnosis of mental retardation or autism spectrum disorder and (ii) indication for inpatient treatment. Caregivers will give written consent (see Appendices) to their HCP to provide personal information to be contacted by the research team.

Participants registered this way (T0, see Fig. 1) receive detailed information about the project (e.g. the technical requirements). After the caregiver’s decision to provide written consent (see Appendices), the inclusion criteria concerning the child’s ADHD or ODD symptoms are checked within the first diagnostic interview (T1). Efforts will also be made to assess patients who drop out of the study.

**Fig. 1 Fig1:**
[figure not shown]
Study design of the ADHD-WASH trial

### Study design

The trial design is described in Fig. 1. The different conditions: web-assisted parent self-help (WASH), WASH plus additional telephone support (WASH+SUPPORT) and treatment as usual (TAU) are compared in a randomized controlled three-arm parallel group design. Approximately *n* = 700 patients are screened for inclusion and exclusion criteria by their HCPs nationwide (T0). If the inclusion criteria are fulfilled within the pre-assessment (T1, *n* = 495), participating families are randomized to one of the three conditions and receive an E-mail with the randomization result as soon as T1 is completed, including the link to the intervention website (WASH and WASH+SUPPORT). Their personal login information is sent separately. If participants have not logged into the website within 5 days, they receive another E-mail, reminding them to use the website and providing the login information again. Participants randomized to the WASH+SUPPORT group are informed about the procedure during an initial telephone call (or E-mail) and receive further telephone assistance (six calls in the first 3 months after completion of T1). An interim assessment (T2) takes place 3 months after the completion of T1, but not before the SUPPORT calls are completed. This makes it possible to record the course of the effects more accurately and to analyze additional effects of the duration of the intervention. The post-assessment (T3, *n* = 396) takes place after a total of 6 months. In all groups, follow-up (T4, *n* = 316) is performed 6 months after completion of the post-assessment. During follow-up (T3 to T4), a health cost diary is completed. Participating caregivers are asked to note every cost (i.e. money, time, additional costs) in a paper-and-pencil protocol. These data are collected during regular telephone calls by research assistants and are transferred into an online survey form.

Additionally, another non-randomized control group of *n* = 80 children aged 6 to 12 years with an ADHD diagnosis is enlisted from a currently running project, ESCA-school [21]. ESCA-school is part of the research network Evidence-based, Stepped Care of ADHD along the life span (ESCA-life) funded by the German Ministry of Education and Research. Participants receive 20 sessions of face-to-face behavior therapy for a period of 6 months. The project has been operating nationwide since January 2016.

### Intervention

The web-assisted parent self-help (https://adhs.aok.de) [22] addresses caregivers of children with ADHD symptoms or oppositional behavior problems. WASH is based on an empirically evaluated treatment program for children with ADHD symptoms and oppositional problem behavior [23] and on a self-help book for parents [19, 24]. This concept has been proven to be effective for families of children with ADHD or other externalizing behavior problems in several studies, both in the form of face-to-face intervention [25] and as telephone-based self-help interventions [19, 26–30].

The structure of the online intervention is shown in Fig. 2. In a matrix design, users are free to take an interest-based approach through the available content of the program. The intervention comprises the following four modules: (1) Psychoeducation (“ADHD – What is it?”), (2) Positive relationship with your child (3) Self-care, (4) Solving behavioral problems. In the fourth module, seven typically problematic situations in the family are presented and users are guided through video-supported examples in seven stages, step by step, by analyzing their own situation with their child and presenting effective methods of change. Caregivers are instructed to use these interventions in everyday life and to document their success within the website. The program consists of tailored (i) text modules, depending on previous (ii) interactive tasks in which users have to assess, for example, their relationship with the child or their own ability to consistently express their individual family rules. Furthermore, (iii) videos and audio recordings are used to make the content easily accessible and to present examples of best practice. Documentation boxes and a personal area, “My Space”, (iv) help to sum up individually relevant aspects and to simplify the adaptation of the WASH recommendations to individual situations. “My Space” serves the purpose of transferring the online information to everyday life (i.e. printable PDF documents analogous to the online tasks).

**Fig. 2 Fig2:**
[figure not shown]
Content and Modules of the ADHD-WASH Program

In the WASH plus SUPPORT group, a trained advisor assists the caregiver with the ADHD parent training. Telephone calls are arranged approximately every 2 weeks (maximum of six 20-min calls within 3 months), during which the advisor discusses the experiences with the program with the caregiver, solves implementation problems and motivates the caregiver to continue his/her work (improve intervention adherence). An individual list of problems (maximum of two) is rated in every call.

### Strategies to improve study adherence

Multiple strategies are applied to retain the families in the study. Participants are given the offer to have the diagnostic results passed on to their HCP. Following T3, families can request information about additional services available to them within the health care and/ or youth welfare system. Participants in the control group (TAU) are provided with analogue material corresponding to the web-based PMT. As far as possible, personnel continuity is aimed at for all assessments in order to create a comforting atmosphere. Families receive “thank-you” postcards after completing T2 and T3 to foster their willingness to participate in the following assessment points.

### Treatment Fidelity

Treatment fidelity in the study, especially in the WASH+SUPPORT group, is assured by (i) a structured and sound training of advisors (guidelines for SUPPORT), (ii) a structured protocol completed by therapists after each session, and (iii) regular supervision of the advisors by senior supervisors.

### Measurements

Data are collected at several *assessment points* before (T1) and after the intervention (T3 & T4) as well as during the *intervention* (T2) (see Fig. 3). Each *assessment point* consists of (i) a clinical interview with the participating caregivers by telephone, as well as (ii) an online survey using the software Lime Survey. At subsequent assessment points (T2 to T4), participants of the intervention groups additionally assess their experience of using the intervention and their satisfaction with it. Further data are generated through (i) assessment by referring HCPs (T1 & T3), (ii) automatically generated utilization data and (iii) caregiver protocols (health cost diary) on the families’ health costs after the intervention.

**Fig. 3 Fig3:**
[figure not shown]
Schedule of enrolment, interventions, and assessments

### Primary and secondary outcomes

#### Primary outcome – blinded clinician

The primary outcome is the externalizing symptomatology in the blinded clinical assessment on German clinical rating scales for ADHD and ODD/CD (*Diagnose Checklist für Aufmerksamkeitsdefizit−/ Hyperaktivitätsstörungen (DCL-ADHS)* and *Diagnose Checklist für Störungen des Sozialverhaltens (DCL-SSV)* [31] based on a structured telephone parent interview (ILF-EXTERNAL) [32]. The blinding is achieved through a second rating of the electronically recorded telephone interview with caregivers. Blinding includes group allocation (three groups) as well as assessment time point (four assessment time points). The externalizing symptoms include ADHD symptoms (18 items) and symptoms of oppositional defiant disorder and conduct disorder (13 items) according to ICD-10 and DSM-5. The original interview guide (ILF-EXTERNAL) was adjusted to the age group, i.e. items for adolescents over 12 years of age were removed.

#### Secondary outcomes – caregiver

The caregiver completes an online survey consisting of the German Symptom Checklist for ADHD (*Fremdbeurteilungsbogen für Aufmerksamkeitsdefizit−/Hyperaktivitätstörungen,* FBB-ADHS) [31], which assesses ADHD symptoms (18 items) and related impairments (five items) as well as the German Symptom Checklist for Oppositional Defiant / Conduct Disorder (*Fremdbeurteilungsbogen für Störungen des Sozialverhaltens,* FBB-SSV) [31], which covers ODD symptoms (eight items), disruptive mood dysregulation disorder (DMDD) symptoms (three items), CD symptoms (six items), characteristics of limited prosocial emotions (11 items), and the child’s impairment due to disruptive behavior problems (five items). The FBB-ADHS and FBB-SSV both consider diagnostic criteria according to the DSM-5 and ICD-10; internal consistency (Cronbach’s Alpha) for the overall symptomology lies at .91, with a range from .68 to .94 for the subscales [31]. A further measure to assess a broad spectrum of emotional and behavioral problems is the German version of the *Child Behavior Checklist for Ages 6–18* (CBCL/6–18R) [33, 34], which has shown satisfactory internal consistencies (a > .70). The child’s quality of life is surveyed through the *KIDSCREEN-10 Index* (10 items) [35], which has demonstrated satisfactory internal consistency (a = .82). Parenting-related measures comprise a German questionnaire for positive and negative parenting behavior (*Fragebogen zum positiven und negativen Erziehungsverhalten,* FPNE) (Cronbach’s Alpha = .91 or .80) to assess functional and dysfunctional parenting practices [36] and the *Depression Anxiety Stress Scale* (DASS; 42 items) to measure parental psychopathology [37], which has shown satisfactory internal consistency (a = .78). Moreover, at T2, T3 and T4, the participants in the intervention groups are asked to report their impression of the intervention through the *User Experience Questionnaire* (UEQ, 26 items, Cronbach’s Alpha ranges from a = .73 to a = .89) [38] as well as their satisfaction with the program using the adapted *Client Satisfaction Questionnaire* (CSQ, 21 items) [39]. Participants who report not having used the program receive questions regarding their non-adherence.

#### Other outcomes

During the use of the intervention, log files from the content management system TYPO3 track the utilization of WASH (i.e. duration and frequency of use of the individual modules). Variables such as first login, last login, number of logins, total login time (in hours), time between logins, number of videos started, number of videos completed, recorded progress etc. are extracted from the system for each user (WASH and WASH+SUPPORT) at T2, T3 and T4. Furthermore, a protocol of all SUPPORT calls (adherence, content of the call, structure of the call etc.) is completed by the advisor after each call (WASH+SUPPORT). Participants in the intervention groups (WASH and WASH+SUPPORT) who have not used the intervention are asked about the reasons for their non-adherence.

Caregivers who withdraw from the study early (dropouts) as well as those who miss out an entire assessment point, are asked to report their reasons for withdrawal or non-attendance and whether they are receiving additional/ alternate provisions. Additionally, ADHD and ODD symptomology are assessed globally (five items from the FBB-SCREEN) [31].

To record the demand for and the cost of health services, participants are led through a health cost diary during the follow-up (for 6 months). Using a protocol of possible costs, they document all treatment events and costs possibly associated with the child’s disorder (for health cost diary, see Becker et al. [40]) and for themselves. Through a combination of specifications and free-text options, it is possible to record costs for health insurance companies as well as private costs.

The following further data are collected from the HCPs: Sociodemographic data about the family at T0 and satisfaction with the study/ intervention at T3 per participant, and again after the last patient out at T4 of a participating practice regarding the overall participation from the HCP’s perspective. Additionally, the psychosocial functional impairment of the child is assessed within the clinical interview with caregivers and directly in the online questionnaire (FBB-ADHS). The satisfaction of referring HCPs is surveyed with a satisfaction questionnaire for medical doctors [41].

### Planned sample size and power calculations

It is assumed that a sample of *n* = 700 patients will be recruited for the initial screening (T0). Based on previous comparable projects, 70% of those in the initial screening are expected to meet the inclusion criteria (T1), so that about *n* = 495 patients will be included and randomized. In online-based self-help studies [15, 16], effect sizes are in the lower to medium range (mostly 0.30 ≤ d ≤ 0.70). Telephone-assisted self-help for parents on the basis of booklets has been found to have moderate effects (0.33 ≤ d ≤ 0.59) [10]. For a comparison of two active conditions (WASH vs. WASH+SUPPORT), rather low to most moderate effects are expected (d = 0.30). Therefore, in this RCT study, the aim is to randomize *n* = 132 (ANCOVA, α = 0.05 two-sided, β = 0.20, correlation pre-post 0.5, 29) [42] participants per group. To compensate for drop-out and cluster effects, an additional 20%, i.e. *n* = 495 (≈3 * 132 * 120%) are included (intention-to-treat set).

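### The sample-size inflation is misstated: 3 × 132 × 120% is 475, not 495, and the expected 20% drop-out to T3 uses the whole allowance, leaving no margin for the cluster effects it is said to cover

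*Protocol article*

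**What the plan says.** All references are to the protocol article.

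- **Planned sample size and power calculations.** For WASH against WASH+SUPPORT, "rather low to most moderate effects are expected (d = 0.30"). The method and its inputs are "ANCOVA, α = 0.05 two-sided, β = 0.20, correlation pre-post 0.5, 29". From these, "the aim is to randomize *n* = 132" participants per group.
- **Same section, inflation.** "To compensate for drop-out and cluster effects, an additional 20"% is added, and the result is given as "n* = 495 (≈3 * 132 * 120%) are included (intention-to-treat set").
- **Study design.** Randomization follows the pre-assessment: "If the inclusion criteria are fulfilled within the pre-assessment (T1, *n* = 495"). "The post-assessment (T3, *n* = 396) takes place after a total of 6 months".
- **Statistical analysis.** Cluster effects are defined as those due to practice or health care provider, and are to be explored. The article gives no intraclass correlation, cluster size or design effect.

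**The concern.** Two statements do not fit the plan's own numbers.

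First, the expression printed for the inflation does not yield the total printed beside it. The gap is about 20 patients, which is more than an approximation sign can cover.

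Second, one allowance is said to serve two purposes, but the expected number at T3 shows that drop-out consumes all of it. A reader would take the trial to have 80% power after some loss to clustering. On the stated calculation it has 80% power only if that loss is nil. This matters when the result is read, above all a null result for WASH+SUPPORT against WASH, the comparison that sets the sample size.

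**Working it through.** **Inputs from the article:** d = 0.30; two-sided α = 0.05; power 80%; pre-post correlation 0.5; 132 per group; three equal groups (implied by 3 × 132); 495 at T1; 396 at T3.

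**1. Base number per group.** ANCOVA with correlation r leaves a variance factor of 1 − r² = 0.75.

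n = 2 × (1.960 + 0.842)² × 0.75 / 0.30² = 130.8, so 131 by the normal approximation.

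With the noncentral t distribution, power is 79.8% at 131 and 80.1% at 132. The stated 132 therefore reproduces, and it is the minimum, with no hidden slack.

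**2. Inflation as printed.**

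- 3 × 132 = 396
- 396 × 1.20 = 475.2 (477 if each arm is rounded up: 132 × 1.20 = 158.4, then 3 × 159)
- 495 / 475.2 = 1.042, so the stated total is 4.2% above its own expression

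**3. Where 495 comes from.**

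- 396 / (1 − 0.20) = 495 exactly, or 132 / 0.80 = 165 per arm
- 495 / 396 = 1.25, so the addition is 25%

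This is the usual correction for 20% drop-out. The total is right for that purpose; the expression beside it is wrong.

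**4. What is left at T3.**

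- 396 / 495 = 0.80, so the expected loss is 20%
- 495 × 0.80 = 396 = 3 × 132
- Margin above the ANCOVA requirement: 396 − 396 = 0 patients

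**5. What clustering would cost if 495 is kept.** The article gives no design effect (DE), so the values below are assumptions. Effective n per arm at T3 is 132/DE, and power is from the noncentral t with standard error √(2 × 0.75 / n). The last column scales the planned effect by √DE.

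| Assumed DE | Effective n per arm | Power for d = 0.30 | Effect detectable with about 80% power |
|---|---|---|---|
| 1.00 | 132 | 80.1% | 0.30 |
| 1.05 | 125.7 | 78.1% | 0.31 |
| 1.10 | 120 | 76.2% | 0.31 |
| 1.20 | 110 | 72.5% | 0.33 |

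The normal approximation gives slightly higher powers (80.4%, 78.4%, 76.5% and 72.9%) and the same picture.

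**The case against.** The strongest reply is that nothing operational is wrong. The figure of 495 stands in the abstract, the Study design section and the sample-size section, and it is the correct total for 20% drop-out. A reader might infer that recruitment could stop at about 475 and so fall short on power. The article does not support that: 475 appears nowhere in it, and 495 is the working target throughout. This part of the reply stands.

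The loss to clustering is also easy to overstate.

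- Patients are randomized individually, so one practice can contribute to several arms. Practice clustering then need not inflate the variance of the group contrast as it would under cluster randomization.
- The primary analysis is a mixed model for repeated measures that excludes only patients without valid baseline values. A child lost before T3 but seen at T2 still contributes, so the information at T3 may exceed that of 396 completers. The article gives no basis for quantifying the gain.

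Both points stand, and they limit the size of the loss. They do not rescue the text: the sample size rests on ANCOVA, credits no gain from the mixed model, and shows no separate reserve for clustering.

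Two further inferences are tempting and should not be drawn. One is that clustering by telephone advisor in WASH+SUPPORT erodes the stated power. The article defines cluster effects by practice or health care provider and never claims to have allowed for advisors. The other is that lower power at T4 contradicts the plan. T4 is a follow-up assessment, and no power is claimed for it.

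**Conclusion.** The point holds in a limited form. The printed expression gives 475, while the stated 495 is 396/(1 − 0.20), a 25% addition. The T3 figure shows that expected drop-out uses all of that addition, so the plan's own calculation does not support the statement that it also compensates for cluster effects. The supportable claim is about 80% power for d = 0.30 at T3, with no explicit margin for clustering.

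The arithmetic rests only on figures in the article. The size of any power loss rests on assumed design effects: about 2 points at 1.05, 4 at 1.10 and 7.5 at 1.20. The true cost of practice clustering is probably towards the low end or below it. It would go too far to say that the trial is underpowered or its target wrong; the documents show only that the claimed reserve is not there. Severity is moderate: a wrong expression and an unsupported statement about the design, with no effect on the target, the estimand or the analysis.

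**What to change.** Keep 495 and restate its derivation, for example: 132/(1 − 0.20) = 165 per arm, 495 in total (25% added), covering 20% drop-out to T3; about 80% power for d = 0.30 at T3, with no separate allowance for clustering. In the same sentence, describe 132 as the number per group needed after drop-out, since 165 per group are randomized.

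Then do one of two things: delete the reference to cluster effects, or keep it and report the power under a stated design effect with its assumed intraclass correlation and cluster size, noting that individual randomization makes that a cautious figure.

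The cost is a few lines of text and a slightly less favourable power statement. No extra patients are needed and the analysis does not change.
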